## Abstract

**Background:**

People with mental disorders face frequent stigmatizing attitudes and behaviors from others. Importantly, they can internalize such negative attitudes and thus self-stigmatize. Self-stigma is involved in diminished coping skills leading to social avoidance and difficulties in adhering to care. Reducing self-stigma and its emotional corollary, shame, is thus crucial to attenuate the negative outcomes associated with mental illness. Compassion-focused therapy (CFT) is a third-wave cognitive behavioral therapy that targets shame reduction and hostile self-to-self relationship and allows for symptom improvement while increasing self-compassion. Although shame is a prominent part of the concept of self-stigma, the efficacy of CFT has never been evaluated in individuals with high levels of self-stigma. The purpose of this study is to evaluate the efficacy and acceptability of a group-based CFT program on self-stigma, compared to a psychoeducation program for self-stigma (Ending Self-Stigma) and to treatment as usual (TAU). We hypothesize that diminished shame and emotional dysregulation and increased self-compassion will mediate the relationship between self-stigma improvements post-therapy in the experimental group.

**Methods:**

This seven-center trial will involve 336 participants diagnosed with a severe mental illness and/or autism spectrum disorder and reporting high levels of self-stigma. Participants will be randomized into one of three treatment arms: 12 week-treatment of compassion-focused therapy (experimental arm), 12 week-treatment of Psychoeducation (active control arm), and TAU (treatment as usual—passive control arm). The primary outcome is the decrease of self-stigma scores on a self-report scale, i.e., ISMI, at 12 weeks. Secondary endpoints include sustainability of self-stigma scores (ISMI) and self-reported scores regarding target psychological dimensions, e.g., shame and emotional regulation, social functioning, and psychiatric symptoms. Assessments are scheduled at pretreatment, post-treatment (at 12 weeks), and at 6-month follow-up. Acceptability will be evaluated via (i) the Credibility and Expectancy Questionnaire at T0, (ii) the Consumer Satisfaction Questionnaire for Psychotherapeutic Services posttreatment and at 6-month follow-up, (iii) attendance, and (iv) dropout rates.

**Discussion:**

This study will evaluate the potential efficacy and acceptability of a group-based CFT program on the decrease of self-stigma and thereby contribute to the continuing development of evidence-based therapeutic interventions for the internalized stigma of mental and neurodevelopmental disorders.

**Trial registration:**

ClinicalTrials.gov NCT05698589. Registered on January 26, 2023

## Administrative information

Note: The numbers in curly brackets in this protocol refer to the SPIRIT checklist item numbers. The order of the items has been modified to group similar items (see http://www.equator-network.org/reporting-guidelines/spirit-2013-statement-defining-standard-protocol-items-for-clinical-trials/).

## Introduction

### Background and rationale {6a}

Severe mental illness (SMI) is defined as a chronic mental disorder that results in severe dysfunction interfering with or substantially limiting one or more major life activities [1]. The definition proposed by the US National Institute of Mental Health includes three dimensions: diagnosis, chronicity, and associated disability [1]. Examples of disorders categorized as SMI include psychotic disorders, mood disorders (i.e., bipolar disorder and recurrent depression), and personality disorders (e.g., borderline personality disorder). The World Mental Health (WMH) Surveys estimate that the annual prevalence of SMI is between 4 and 6.8% of adults [2]. Despite the existence of pharmacological and psychological treatments with proven efficacy in reducing symptoms, the social inclusion of people with SMI remains dramatically reduced.

It is now widely recognized that factors other than symptoms of the condition and adverse effects of pharmacological treatments can interfere with the prognosis and the social inclusion of people with psychiatric disorders. Specifically, stigmatizing attitudes and behaviors that people with SMI face from others can negatively impact the course of their illness [3–5]. In response to stigmatizing behaviors, they tend to isolate themselves and avoid medical care, as well as social and professional situations, with the risk of hindering care and the overall process of personal recovery and integration into society [6]. Relatedly, SMI is the first cause of occupational disability as well as one of the first causes of unemployment [7] and work absenteeism in Europe [8].

The internalization of stigma, i.e., self-stigma, is thought to be one of the main causes of the reduced social inclusion of people with SMI [9–11]. Self-stigma is defined as the process by which an individual internalizes negative messages about their own social group and applies them to themselves [12]. This phenomenon, which is strongly associated with negative emotions (i.e., shame) [13], self-critical thoughts, and a significant fear of public stigma—that is, stigmatizing attitudes and behaviors from others [3]—prevents individuals from fulfilling and pursuing their life goals [14]. In particular, self-stigma is involved in diminished coping skills that lead to social avoidance and difficulties in adhering to care [7]. Considered as the affective component of self-stigma [13], shame is highly associated with negative self-evaluation and self-criticism, greater severity of clinical presentations, and impeding treatment [15–17]. In addition to increasing the risk of psychopathology, shame can thus be a hindrance to the effectiveness of treatments as it influences the expression of symptoms and the patient’s ability to disclose painful information and to seek help, and it can promote several types of avoidance, such as dissociation and therapy drop-out [16].

Given the relationship between self-stigma and personal recovery in people with SMI, a growing number of studies have focused on this issue in recent years. For instance, a recent systematic review reported high levels of self-reported self-stigma in people with SMI but also in neurodevelopmental conditions such as autism spectrum disorder (ASD) [18]. In addition, recent meta-analyses and systematic reviews have highlighted the negative consequences of self-stigma on multiple aspects associated with the quality of life and the well-being of patients. For example, self-stigma in SMI and ASD is related to lower self-esteem and a reduced feeling of self-efficacy [19, 20], as well as lower levels of quality of life, increased risk of depressive and anxious symptoms, and increased hopelessness [19, 21, 22]. From a personal recovery perspective, self-stigma is linked to impaired social functioning, high levels of social withdrawal, high rates of unemployment, and reduced motivation to engage in pro-health behaviors, i.e., poorer physical health and poorer treatment adherence [18, 23–25]. Reducing self-stigma and its emotional corollary, i.e., shame, is thus crucial to attenuate the disability associated with mental illness and improve the quality of life and social inclusion of people with SMI and ASD.

Over the last decade, research focusing on the social inclusion and personal recovery of people with SMI and ASD has focused increasingly on psychosocial treatments aimed at reducing self-stigma. However, psychological treatments for the reduction of self-stigma remain rare, and recent meta-analyses and systematic reviews have highlighted several methodological pitfalls in existing studies assessing the feasibility and efficacy of interventions (e.g., lack of randomized controlled studies) [26, 27]

Interventions aimed at reducing self-stigma can be classified into four categories (i) psychoeducation, (ii) second-wave cognitive behavioral therapies (CBT) aiming to change beliefs (internalized stereotypes) related to mental illness, (iii) interventions targeting the disclosure of one’s mental illness, and (iv) multi-component interventions. On average, the existing interventions are composed of 10 sessions and are carried out in groups [26–29].

Among the interventions designed to reduce self-stigma in people with SMI, group psychoeducation has been the most studied [26–28]. In particular, the Ending Self-Stigma (ESS) program [12, 29, 30] is among the rare interventions whose efficacy has been tested via a randomized controlled trial (RCT) [30]. The ESS program is a 9-session manualized group intervention during which participants learn skills aimed at reducing self-stigma. Sessions consist of learning cognitive strategies (e.g., identifying and changing self-stigmatizing thoughts) and problem solving. In their study, Lucksted et al. [30] compared this intervention to treatment as usual (TAU) and found an immediate improvement in the alienation and stigma resistance subscales of the Internalized Stigma of Mental Illness Scale (ISMI) [31] but no improvement on the total self-stigma score. Moreover, the effects were modest, failed to be significant at 6 months of post-treatment follow-up, and the authors reported a very high drop-out rate and low attendance (only 43% of participants attended at least 7 sessions). Similar results suggesting the high attrition rate of the ESS have been reported in a more recent study [12]. The latter indicates no superior effects of ESS compared to a nonspecific health and well-being program. These different trials emphasize the limitations of the ESS (e.g., the attrition rates, the inconclusive results when the ESS was compared to an active control group, and the lack of sustainability of self-stigma outcomes at follow-up). Given that the affective component of self-stigma, i.e., shame, was not targeted by the ESS, we hypothesize that high levels of shame lingered post-therapy leading both to social avoidance and high rates of drop-out.

Overall, despite the aforementioned limitations, psychoeducation programs such as the ESS [30] remain recommended in recent meta-analyses and systematic reviews as they cumulated the highest level of evidence for reducing self-stigma associated with SMI. The aim of our compassion-focused intervention is to address the main limitations of more traditional approaches that do not address the shame associated with self-stigma. To do so, unlike traditional CBT and psychoeducation programs, our intervention aims to directly target the affective component of self-stigma, i.e., shame [13, 17], through compassion-focused therapy (CFT) [16, 32].

CFT is part of third-wave CBT. Importantly, CFT specifically targets shame reduction and hostile self-to-self relationships and allows for symptom improvement [33] while increasing self-compassion, a major resilience factor [34]. In CFT, compassion is defined as a motivation that orients to *a sensitivity to suffering in self and others with a commitment to try to alleviate and prevent it* [35]. CFT builds on traditional CBT principles and blends empirical knowledge from affective neuroscience, social and developmental psychology, and mindfulness. CFT has gathered a large body of evidence in the treatment of shame and self-blame in a wide range of clinical settings [e.g., [16, 33, 36–40]].

Although CFT focuses on the treatment of shame-related difficulties, few studies have focused on the relationship between self-stigma and self-compassion. In a recent study, Wong et al. [11] provided a theoretical framework emphasizing the potential benefits of CFT for self-stigma. According to the authors, self-compassion could buffer the negative effects of stigma by facilitating more social resources and increasing the willingness to ask for help [11]. Therefore, given its focus on the psychological processes and affective aspects of self-stigma, CFT may be more effective than existing interventions in the reduction of self-stigma and shame [11]. More specifically, CFT targets emotions and attitudes (i.e., shame and avoidance) directly and could address the gaps of existing interventions, which focus mainly on cognitive (beliefs and stereotypes) changes. Supportive of this view, numerous social psychology studies suggest that it is necessary to target the affective dimensions of stigmatizing attitudes (i.e., shame) to achieve lasting behavioral changes [4, 41, 42]. Indeed, emotions and feelings are better predictors of change in behaviors than beliefs (for reviews, see [43, 44]).

The purpose of our study is to evaluate the efficacy and acceptability of a transdiagnostic CFT group for self-stigma compared to ESS [30] and treatment as usual (TAU). CFT has been found to be feasible and to reduce shame in SMI including personality disorders [37], patients with psychosis [45, 46], as a transdiagnostic group [47] and, in a pilot study led by our group, in patients presenting with SMI and ASD [48]. However, CFT has not been used to specifically target self-stigma and shame in this population. Our adaptation of CFT aims to address the limitations of existing self-stigma reduction programs such as the ESS [e.g., [30]], i.e., (i) lack of superior effects when compared to active control interventions, (ii) low attendance and high dropout rates, and (iii) lack of long-term effects, which can be attributed to the fact that interventions aimed at deconstructing beliefs and did not target shame.

#### Objectives {7}

The primary objective of our study is to evaluate the efficacy of a 12-week CFT group in decreasing self-stigma associated with severe psychiatric disorders and ASD by comparing its immediate effects to the effects of the Ending Self-Stigma (ESS) psychoeducation program [29] and to TAU.

The secondary objectives of our study are as follows:1. To evaluate the maintenance of effects on self-stigma scores in the three groups of treatment (CFT, ESS, and TAU) at 6-month follow-up (V2)2. To assess the effects of treatment (CFT, ESS, and TAU) at baseline (V0), post-treatment (V1), and at 6 months follow-up (V2) on target psychological dimensions (shame, self-compassion, emotional regulation, automatic avoidance tendencies toward mental illness)3. To assess the effects of treatment (CFT, ESS, and TAU) at baseline (V0), post-treatment (V1), and at 6 months follow-up (V2), on social functioning and psychiatric measures (psychiatric symptoms, depression, anxiety and stress, social functioning, access to care, recovery, functional remission)4. To assess the psychological factors mediating (shame, self-compassion, and emotional dysregulation) the efficacy of CFT on the self-stigma measure (V1)5. To evaluate the acceptability of the active interventions (CFT and ESS): pretreatment (V0) via a treatment credibility measure, during treatment via attrition rate, session attendance and group cohesion, and post-treatment (V1) via patient satisfaction and treatment side effects In addition, in the coordinating center, qualitative interviews will assess the acceptability of the active interventions.

### Trial design {8}

This project is a seven-center, prospective, randomized, parallel-group, controlled superiority trial with three arms: an experimental arm with 12 CFT group sessions; an active control arm with 12 psychoeducation-ESS group sessions, and a passive control arm consisting of TAU. The allocation ratio is 1:1.

## Methods

### Study setting {9}

The COMPASS trial will be performed in 7 French national centers (Strasbourg University Hospital, Psychotherapeutic Center of Nancy, le Vinatier Hospital, Montpellier University Hospital, Bordeaux University Hospital, Clermont-Ferrand University Hospital, Reims University Hospital). Patients will be recruited by psychiatrists or psychologists in the seven centers, where data will be collected during the trial.

### Participants

#### Eligibility criteria {10}

The included centers are nationally recognized as central coordinators of care (within a recovery of mental disorders model) in their respective regions.

## Inclusion criteria

Patients must meet the following criteria to be eligible for the study:- Patients≥ 18 years of age- Patient affiliated to a social health insurance plan (beneficiary or beneficiary’s family)- Patient with one or several diagnoses of chronic psychiatric disorder (schizophrenia, schizoaffective disorder, bipolar disorder, recurrent major depression, borderline personality disorder) or a neurodevelopmental disorder (autism spectrum disorder) treated as an outpatient or in a day hospital- CGI-Severity score < 6, assessed by the psychiatrist [49]- ISMI score indicating moderate to high self-stigma (> 2) [50]

## Non-inclusion criteria

They will not be eligible for the study if any of the following applies:- Patient in an exclusion period determined by a previous or ongoing study- Patient participating in an interventional study involving psychotherapy or an experimental drug- Patient in acute episode of their disorder according to the CGI Severity score- Patient in a medical emergency or immediate life-threatening situation- Patients with an intellectual disability (IQ < 70) estimated via the fNART [51]- Legal issues: care under constraint or patient deprived of freedom because of a judicial - measure- Patient who does not speak and read French sufficiently

## Inclusion criteria for individuals who will perform the interventions

- The facilitators of both psychotherapies are mental health professionals or peer support worker.- In each psychotherapy group of 8 patients, one of the facilitators is a senior psychologist.

Senior psychologists are trained in either (i) CFT for the experimental arm or (ii) the ESS program for the active control arm

### Who will take informed consent? {26a}

Patients diagnosed with one or several diagnoses of chronic psychiatric disorder (schizophrenia, schizoaffective disorder, bipolar disorder, recurrent major depression, borderline personality disorder) or ASD, treated as outpatients or in a day hospital, will be screened for eligibility to participate in this study.

After at least 2 weeks of reflection after receiving study information during a routine visit, patients (or their legal representative) are invited to meet with the research psychiatrist to discuss any remaining questions and sign the informed consent.

### Additional consent provisions for collection and use of participant data and biological specimens {26b}

This trial does not involve collecting biological specimens for storage.

### Interventions

#### Explanation for the choice of comparators {6b}

There are two control groups (active and passive control): The active control group consists of a 12-week treatment of ESS psychoeducation, because recent meta-analysis and systematic review recommended this treatment [30]. The passive control group consists of 12 weeks of treatment as usual (TAU—e.g., visits in the context of a day hospital or as an outpatient). Given the limited number of interventions targeting internalized stigma in France, TAU is the comparator of choice.

### Intervention description {11a}

Participants randomized to the experimental arm and the active control arm will begin the intervention (CFT or ESS) within 1 month, to allow for the formation of a group of 8 individuals for each active arm.

Both therapies (CFT and ESS) will follow the same modality: groups of 8 participants, 12 sessions of therapy facilitated by 2 co-therapists (one senior psychologist and one mental health professional or peer support worker). The duration of each session will be 2 h including a 15-min break. For both therapies, a whiteboard and therapy manuals (booklets for the participants with summaries of key information and worksheets and booklets for the facilitators) will be provided with aims and contents for each session and examples of verbatim for the therapist. Both therapies will include in-between session practices for the participants.

Participants randomized to the TAU arm will pursue their routine care (including visits to their psychiatrist and other treatment modalities delivered in their routine care with the exception of specific psychotherapies, such as CBT).

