## Passive control arm (TAU)

Participants will not participate in any intervention aimed at reducing self-stigma. They will continue their usual treatment which might include weekly visits to their psychiatrist. Participants and therapists in each center will receive, after the study period, access to the ESS notebook.

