### Relevant concomitant care permitted or prohibited during the trial {11d}

During the trial, all concomitant treatments are accepted except CFT and CBT (including psychoeducation) for self-stigma. A participant starting psychotherapy in parallel to their participation in the protocol will be kept in the group for ethical and clinical reasons. Their data will be excluded from the study.

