### Randomization

The investigator (psychiatrist) will then confirm the eligibility of the patient to another investigator (psychologist or nurse) of their team, who will be in charge of the randomization of the patients on the CleanWEB platform. This will ensure a blind assessment of the post-treatment evaluation by the psychiatrist at V1 and V2 (i.e., the BPRS and Mini-FROGS scales).

Patients will be randomized by the psychologist or the nurse into one of the following arms:Experimental arm: 12 week-treatment of compassion-focused therapy (CFT) (i.e., psychoeducation on the model, experiential in-session exercises, and in-between session compassion practices, video-guided practices). Sessions cover several topics: psychoeducation on compassion from an evolutionary and neuroscientific perspective, emotion regulation skills (especially shame), and compassion practices.Active control arm: 12 week-treatment of the psychoeducation program *Ending Self-Stigma* (ESS) [29]. Sessions cover topics such as modifying self-stigmatizing thoughts and homework.Passive control arm: patients follow their usual care, i.e., TAU (e.g., psychiatric, psychological, day hospital), which will be unchanged during the 12-week period. Following their 10-month participation in the study, they will be given access to the written material used for the ESS.

Participants will then be asked to complete self-report questionnaires assessing self-compassion, shame, depression, anxiety, barriers to care, social functioning, recovery, and functional remission. During this visit, the cognitive task assessing avoidance/approach attitudes toward mental illness (VAAST) will also be carried out by the psychologist or the nurse.

Two individual sessions with a clinician (engagement phase) will be conducted between V0 and the beginning of CFT and ESS (i.e., within 1 month). These sessions will include motivational interviewing techniques and case conceptualization aimed at increasing the participant’s level of engagement in therapy.

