### Plans to promote participant retention and complete follow-up {18b}

Patients enrolled in the study will receive a compensation (i.e., 100 euros) at the end of the last visit with the psychiatrist. To receive the compensation, participants must have completed the visits V1, V2, and V3.

For patients in the three arms, in case of premature termination of participation in the study by decision of the investigator or the patient/guardian, the self-report questionnaires including the ISMI will be administered one last time to the exiting participant, if the patient/guardian agrees. A semi-structured evaluation interview will also be conducted. For patients who quit the study prematurely, all data collected before the decision to interrupt the study will be analyzed.

A participant starting psychotherapy in parallel to their participation in the protocol will be kept in the group for ethical and clinical reasons. Their data will be excluded from the study.

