Indeed, if our 12-session group program produces a significant decrease in self-stigma and shame scores and improves participants’ social inclusion in a long-term perspective, it could become an empirically assessed viable option specifically suited to the needs of people presenting with SMI or ASD, whose quality of life is diminished due to high self-stigma. Moreover, in terms of format and content, this 12-session-manualized-group CFT has many advantages. Indeed, by targeting key transdiagnostic psychological processes—i.e., self-stigma and shame—it can increase the feasibility and dissemination of the intervention to a high number of clinical contexts (e.g., community health centers, different clinical populations).

Our study protocol presents some limitations. First, the distribution of diagnostic categories might present some inevitable variability across different hospital centers involved. However, our purpose is to propose a transdiagnostic intervention. Relatedly, facilitators’ backgrounds will vary depending on the centers, with possibly different training backgrounds and clinical experiences. To account for this limit, all group facilitators will be trained by the coordinating center clinical team during a 3-day-training specific to each intervention. Second, though concomitant psychotropic medications as well as the use of adjunctive therapeutic means (e.g., self-help or counseling) will be controlled in our study, participants will not be instructed to avoid making use of them. While this might be a potential confound in the current study design, the restriction of therapeutic options would also pose an ethical concern, reduce referrals to the study and also be a threat to external validity. Therefore, by monitoring therapeutic (i.e., medication or counseling) use throughout the trial, the current study seeks to balance the internal and external validity and improve the feasibility of the study while efficiently addressing its hypotheses.

If our innovative group CFT program can effectively reduce self-stigma and shame, it may facilitate the social inclusion of a large number of people with severe mental illness and/or ASD and significantly improve their quality of life and their physical and mental health by reducing barriers to access care.

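### One sentence takes psychotherapy such as CBT out of routine care in the TAU arm only, against the protocol's other rules on permitted care

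*Protocol article*

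**What the plan says.** Four places in the protocol article describe what care may run alongside the trial.

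- **Intervention description {11a}**, for TAU participants only: they keep their psychiatric visits and "other treatment modalities delivered in their routine care with the exception of specific psychotherapies, such as CBT".
- **Passive control arm (TAU)**: "Participants will not participate in any intervention aimed at reducing self-stigma. They will continue their usual treatment".
- **Relevant concomitant care {11d}**, with no arm named: "all concomitant treatments are accepted except CFT and CBT (including psychoeducation) for self-stigma".
- **Randomization**, under the TAU arm: "patients follow their usual care, i.e., TAU (e.g., psychiatric, psychological, day hospital), which will be unchanged during the 12-week period".

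Three further places bear on the question.

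- **Non-inclusion criteria** exclude a "Patient participating in an interventional study involving psychotherapy or an experimental drug".
- **Items {11d} and {18b}** say that "A participant starting psychotherapy in parallel to their participation in the protocol will be kept in the group for ethical and clinical reasons", and that such a participant's data are left out of the study.
- **The Discussion** says that adjunctive therapy is not forbidden to participants, and that the trial will balance internal and external validity "by monitoring therapeutic (i.e., medication or counseling) use throughout the trial".

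**The concern.** Item {11a} defines what each arm receives. Its sentence on TAU removes a class of treatment, psychotherapy such as CBT, whatever that treatment is for. The other statements remove only treatment aimed at self-stigma, or say that usual care goes on as before. A site reading {11a} alone could conclude that a TAU participant should not be in CBT for, say, recurrent depression. A site reading {11d} would let it continue.

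TAU is one of the two comparators in the primary objective. Participants and care providers know the allocation, and the ISMI is self-reported. If ongoing psychotherapy were withheld in TAU but allowed in CFT and ESS, the arms would differ in background treatment as well as in the assigned programme, and the comparator would no longer be usual care. Provided such therapy lowers ISMI scores, or stopping it raises them, the difference would favour both active arms over TAU. With seven centres, practice could also vary by site.

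**Working it through.** No figure in the plan depends on this point, so there is none to reproduce. The check is a comparison of the texts.

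**Step 1. The rules side by side.**

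| Section | Arm covered | What is barred | What continues |
|---|---|---|---|
| Intervention description {11a} | TAU only | Specific psychotherapies such as CBT, any indication | Other routine care |
| Passive control arm (TAU) | TAU | Interventions aimed at self-stigma | Usual treatment |
| Concomitant care {11d} | None named, so all | CFT and CBT (with psychoeducation) for self-stigma | All other treatments |
| Randomization | TAU | Nothing named | Usual care, psychological care included, unchanged for 12 weeks |

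The clash is sharpest between {11a} and {11d}. It is also clear against the Randomization text if the psychological care there includes CBT, and milder against the TAU section, which bars a narrower set and otherwise continues treatment.

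**Step 2. Which participants are affected.**

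- CBT for self-stigma: barred under {11a}, the TAU section and {11d}. No conflict.
- Psychotherapy newly started during the trial: {11d} and {18b} keep the participant in the group and drop the data, whatever the arm. No arm difference arises here.
- CBT or similar therapy for another target, already under way at V0: excepted by {11a} in TAU, accepted by {11d} in every arm. This is the conflict.

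**Step 3. Whether another rule settles the third case.**

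- The non-inclusion criterion concerns psychotherapy within an interventional study. A patient in routine CBT is eligible.
- The data-exclusion rule speaks of a participant *starting* psychotherapy, not of one already in it.
- No sentence orders ongoing therapy to be stopped. The weight of the text favours continuation, which makes {11a} the outlier, but the conflicting sentence remains.

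**Step 4. Scope.**

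- Participants under the TAU-only wording: 112 / 336 = 33.3%. This is the whole TAU arm, not the subset already in psychotherapy.
- Three arms give 3 pairwise contrasts. Two involve TAU (CFT-TAU and ESS-TAU).

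**Step 5. Size.** If every site applied {11a}, the shift in an active-TAU contrast would be about *f* × *e*, where *f* is the share of participants in such therapy at V0 and *e* is its effect on ISMI at V1. The protocol gives neither. Purely to show scale, assume *f* from 5% to 30% and *e* from 0.05 to 0.25 points:

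- low end: 0.05 × 0.05 = 0.0025 points;
- high end: 0.30 × 0.25 = 0.075 points.

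From the means in Sample size {14}, the planned V1 differences from TAU are 2.43 − 2.10 = 0.33 (CFT) and 2.43 − 2.20 = 0.23 (ESS). The range is an assumption, not an estimate. The shift is zero if no site applies {11a} or if *e* is zero.

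**The case against.** The best defence is that the {11a} wording sits in a parenthesis describing what routine care contains and instructs nobody to stop anything. Item {11d} is the section dedicated to permitted and prohibited care, so it should govern, and the {11a} phrase is probably loose shorthand for it. The Randomization text mentions psychological care without naming CBT, so that clash can be argued away, and the Discussion leans towards not restricting treatment. New psychotherapy is handled alike in all arms, so only a small group remains, at sites that read {11a} strictly. The direction of bias is also assumed: the Background reports that even ESS did not improve the total ISMI score against TAU in its randomised trial. Finally, this is a condensed article, and sites may work from a fuller document.

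Much of this stands. The affected group is narrow, its size is unknown, the bias may be nil, and {11d} is very likely the intended rule. What does not fall away is the text itself. The {11a} phrase is worded as an exception, for one arm, without the self-stigma limit, and no statement gives {11d} precedence. Two stated rules that disagree are an error in the document shown, not a detail left out for brevity.

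**Conclusion.** The inconsistency is real and should be fixed. As written, {11a} restricts background psychotherapy in TAU alone, while {11d} sets a narrower bar for all arms and the two other TAU descriptions continue usual care. The open case is a TAU participant already in CBT or similar therapy at V0 for something other than self-stigma.

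Confidence in the textual conflict is high. Any bias is conditional on sites following {11a}, on such participants being present, and on the therapy affecting ISMI. Its size cannot be estimated from the protocol. If all sites follow {11d}, there is no arm difference.

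**What to change.** Delete the exception in {11a}, or replace it with the {11d} rule, so that one rule on concomitant psychotherapy applies identically to CFT, ESS and TAU from V0 to V2. State in that rule that psychotherapy already ongoing at V0 and not aimed at self-stigma may continue in every arm. Extend the monitoring promised in the Discussion, which names medication and counselling, so that it expressly covers ongoing psychotherapy, and report it by arm.

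The cost is one sentence of protocol wording and a note to sites; monitoring of concomitant care is already planned. The Trial status section says that enrolment had not begun, so on that timing the rule could hold from the first participant. The one drawback is that, with psychotherapy clearly continuing in all arms, the CFT-TAU difference may be slightly smaller; it would then be a comparison with genuine usual care.
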